## Methods

### Study Design

This study will employ an open-label randomized controlled trial design to investigate the efficacy of a web-based psychotherapy program in treating anxiety and depressive symptoms in patients receiving oncologic and palliative care. Participants will be randomly allocated to receive either the web-based psychotherapy program or treatment as usual (TAU) for 8 weeks. This study has been registered on ClinicalTrials.gov (protocol# NCT04666974).

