### Participants

Patients (n=60) diagnosed with depressive or anxiety disorders due to another medical condition in the context of oncologic or palliative care will be recruited through referrals from the Kingston Health Sciences Centre (including the cancer center), Providence Care Hospital, family physicians, other health care providers, and self-referrals in Kingston (Ontario, Canada). After consenting to take part in the study, a complete assessment will be performed by one of the psychiatrists on the team to confirm the diagnosis. Inclusion criteria are an age of 18-55 years at the start of the study; a diagnosis of depression or anxiety secondary to a general medical condition (in the context of oncologic or palliative care conditions), using the Diagnostic and Statistical Manual of Mental Disorders, 5th edition, by one of the psychiatrists on the team; competence to consent and participate in the study; ability to speak and read in English; and consistent and reliable access to the internet. Exclusion criteria are having acute hypomanic or manic episodes, acute psychosis, severe alcohol or substance use disorder, active suicidal or homicidal ideation, or currently receiving or having received CBT in the past year. Participants will then be randomly assigned to two groups: TAU control group (ie, medication, psychiatric consultation, referrals to in-person activities or groups, etc) or the e-CBT (e-CBT + mindfulness + problem solving + TAU) treatment group. Participant allocation will be equally stratified (e-CBT, n=30; TAU, n=30).

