### Data Analysis

Initially, all data will be examined for missing, nonsensical, and outlying variables. Missing data will be treated as missing and not imputed (ie, will be analyzed on a per-protocol basis). Given the likelihood of participant dropout or withdrawal, participants have been purposely oversampled to obtain meaningful and statistically significant results at the end of the study. Based on previous experience with CBT and e-CBT in similar patient populations, the anticipated dropout is up to 30% by the end of the phases. However, the remaining individuals will be able to provide significant information regarding changes in their symptoms. Given that several outcomes will be considered, it is difficult to calculate a single sample size or provide a specific power calculation. However, using the 9-item Patient Health Questionnaire as an example, as it is common to all participants, a 30% change is considered clinically significant. Therefore, a sample size of 20 participants in each arm of the study would be sufficient for obtaining significant results with *P*=.05 and a power of 0.95.

Baseline and demographic data from individuals who drop out will be compared to those who finish identifying any fundamental differences between completers and noncompleters. Linear regression models will be used to compare treatment and control outcomes while controlling for demographic variables such as age and gender.

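### The power of 0.95 with 20 per arm does not follow from a 30% PHQ-9 change; between arms it requires a difference of about 1.17 SD

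*Protocol article*

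**What the plan says.** The protocol article describes a randomised comparison (Study Design): "This study will employ an open-label randomized controlled trial design to investigate the efficacy of a web-based psychotherapy program". Allocation is equal (Participants): "Participant allocation will be equally stratified (e-CBT, n=30; TAU, n=30". The Participants section describes TAU as active care that includes medication, psychiatric consultation and referrals.

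The sample size reasoning is in Data Analysis. It first concedes that, with several outcomes, "it is difficult to calculate a single sample size or provide a specific power calculation". It then takes the PHQ-9 as an example, says that "a 30% change is considered clinically significant", and draws the conclusion that "a sample size of 20 participants in each arm of the study would be sufficient for obtaining significant results with" a 5% level "and a power of 0.95". It expects dropout of up to 30%.

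The same section sets out the analysis: "Linear regression models will be used to compare treatment and control outcomes while controlling for demographic variables such as age and gender".

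**The concern.** The conclusion is presented as a consequence of the 30% figure alone, and a percentage change has no standardised size. To become an effect that a two-arm comparison can be powered for, it needs three further quantities: the baseline mean (to turn 30% into points), the SD (to turn points into SD units), and the change expected under TAU (to turn change in one arm into a difference between arms). The article gives none of them.

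The third quantity matters most. A 30% improvement under e-CBT equals a 30% difference between arms only if TAU patients do not change at all. The Procedures section allows for improvement under TAU, because control patients are offered e-CBT after 8 weeks only if they are still significantly symptomatic relative to baseline.

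This is the only numerical justification given for the sample size. If the between-arm power is well below 0.95, a reader who relies on that figure will give a non-significant result more weight than it can bear.

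**Working it through.** **Inputs from the article.** 20 evaluable per arm, level 0.05, power 0.95, a 30% PHQ-9 change, 30 randomised per arm, dropout up to 30%. Sidedness is not stated; two-sided is assumed.

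**Assumed inputs, not in the article.** Baseline PHQ-9 mean of 10, 12, 15 or 18; SD of 4, 5 or 6 points; TAU improvement of 0% or 10%; correlation r between baseline and follow-up of 0.5 or 0.7.

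**1. Can the stated figure be reproduced?** No. Without a mean and an SD, the 30% gives no effect size. The check is therefore run in reverse, to find the effect that 20 per arm and 0.95 power imply.

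**2. Implied between-arm effect.** Normal approximation: d = (z for 0.975 + z for 0.95) × √(2/n) = (1.960 + 1.645) × √(2/20) = 1.14. The exact two-sided t-test gives:

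| Evaluable per arm | d for 80% power | d for 95% power |
|---|---|---|
| 20 | 0.91 | 1.17 |
| 30 | 0.74 | 0.95 |

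A one-sided t-test with 20 per arm would need d = 1.06 for 95% power.

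**3. What this asks of the 30%.** If the whole 30% is the between-arm difference, d = 0.30 × baseline / SD. Reaching 1.17 requires an SD of at most 0.30 / 1.17 = 0.256 × baseline, which is about 3.85 points at a baseline of 15.

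**4. Power with 20 per arm, whole 30% credited to the between-arm difference** (exact t-test, d in brackets):

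| Baseline (difference) | SD 4 | SD 5 | SD 6 |
|---|---|---|---|
| 10 (3.0 points) | 0.64 (0.75) | 0.46 (0.60) | 0.34 (0.50) |
| 12 (3.6 points) | 0.79 (0.90) | 0.60 (0.72) | 0.46 (0.60) |
| 15 (4.5 points) | 0.93 (1.13) | 0.79 (0.90) | 0.64 (0.75) |
| 18 (5.4 points) | 0.99 (1.35) | 0.91 (1.08) | 0.79 (0.90) |

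One of the 12 cells reaches 0.95. Outside this grid, baseline 20 with SD 5 gives d = 6/5 = 1.20 and power 0.96.

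**5. Allowing for TAU.** If e-CBT improves by 30% and TAU by 10%, the difference is 20% of baseline. In the central case (baseline 15, SD 5), d = 3.0/5 = 0.60 and power is 0.46.

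**6. Number needed for 0.95 power.** At d = 0.90, 34 per arm; at d = 0.60, 74 per arm.

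**7. Adjusting for baseline PHQ-9.** The residual SD shrinks by √(1 − r²). In the central case, d = 0.90/√(1 − 0.25) = 1.04 gives power 0.89 at r = 0.5, and d = 0.90/√(1 − 0.49) = 1.26 gives 0.97 at r = 0.7. With 10% TAU improvement the corresponding powers are 0.57 and 0.74.

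**8. Dropout.** 30 × 0.70 = 21 remain per arm, so the target of 20 is consistent with the recruitment plan. This part is sound.

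**The case against.** Four points can be made for the plan.

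*The article condenses a fuller document, and the SD, baseline mean and TAU change may be there.* This stands as far as it goes: their absence alone would not be a finding. It does not rescue the inference actually printed, which moves from the 30% to 0.95 with nothing in between.

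*The text hedges.* It says that a specific power calculation is difficult and offers the PHQ-9 only as an example. This softens the claim, but the passage still ends on a definite sample size and a definite power.

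*The analysis is an adjusted regression, not a t-test.* Adjustment for the baseline score could lift central power to 0.89 or 0.97. The baseline score is measured and the covariate list is open-ended. However, only demographic variables are named, so the article does not commit to this gain, and with modest TAU improvement it would not be enough.

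*Some inputs do give 0.95.* This is correct. A high baseline with a small SD reaches it, so the figure cannot be called false.

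A reader might also infer that the number came from a before-after test within one arm, because a paired test with n = 20 reaches 0.95 at 0.85 SD of the change. The documents do not support that inference. No test is named, and the paired reading rests on an SD of change that is not given either: at baseline 15, paired power is 0.97 with an SD of change of 5 but 0.89 with 6. Which calculation produced the figure cannot be identified.

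**Conclusion.** The concern holds as a failure of derivation. The stated power does not follow from the stated premise, and for the analysis as described it is probably optimistic. What can be said without further assumptions about the PHQ-9 is that 0.95 power with 20 per arm needs about 1.17 SD between arms (unadjusted, two-sided 5%). The range of 0.34 to 0.99, the central 0.79 and the 0.46 with TAU improvement all rest on the assumed baselines, SDs and TAU change listed above.

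It would go too far to say that the trial lacks 95% power: favourable inputs reach it, and so could baseline adjustment. The figure is unsupported, not disproved. This should be fixed, but it does not alter the recruitment target, the allocation or the dropout allowance.

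**What to change.** Withdraw the 0.95 claim from Data Analysis and replace it with a statement such as:

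> With 20 evaluable per arm (two-sided 5%, unadjusted) the trial has 95% power for a between-arm difference of 1.17 SD and 80% power for 0.91 SD; with all 30 per arm analysed, 80% power is for 0.74 SD.

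Express the target as a between-arm PHQ-9 difference in points, and state the SD and the TAU change assumed. If power is to be quoted for a baseline-adjusted analysis, name baseline PHQ-9 as a covariate and give the assumed correlation. An expected confidence interval width, or a sentence on how a non-significant result will be read, would be useful but is optional.

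The cost is a change of wording and a less favourable stated power. No extra recruitment is needed.

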### Outcome Evaluation

The primary outcome measure will be the progression or regression of our participants’ mental health symptoms. Outcome measures will include the scores of the following standardized questionnaires: Functional Assessment of Cancer Therapy-General, 9-item Patient Health Questionnaire, 7-item Generalized Anxiety Disorder, 14-item Resilience Scale, and the Quality of Life and Satisfaction Questionnaire. Assessments will be completed upon study entry and after weeks 4 and 8 of the program. Other behavioral data regarding patients’ interaction and engagement with their therapy (ie, number of logins per day and amount of time spent on each session) will be collected directly through the OPTT to obtain further insight. We hypothesized that the level of patient engagement may have predictive power in therapy outcomes.

The anticipated quantitative outcomes include a progression of questionnaire scores, high frequency of logins, and high frequency of logins during nonbusiness hours. The anticipated qualitative outcome is positive feedback from participants receiving e-CBT and health care providers.

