## Results

This study received funding in August 2020 and ethics approval from the Queen’s University Health Sciences and Affiliated Teaching Hospitals Research Ethics Board (file# 6031471) in February 2021. Participant recruitment has been conducted through social media advertisements, physical advertisements, and physician referrals. To date, 11 participants (e-CBT, n=5; TAU, n=4; dropout, n=2) have been recruited. Data collection is expected to conclude by December 2021, and data analysis is expected to be completed by January 2022. Linear regression (for continuous outcomes) will be conducted with interpretive qualitative methods. All protocols and results have been, and will be, reported using the GUIDED and TIDieR Report Checklists and Guidelines (Multimedia Appendices 1 and 2).

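### The stated regression controls only for demographic variables; adding the baseline value of the same questionnaire score would gain precision and deal with chance baseline imbalance at no data cost

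*Protocol article*

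**What the plan says.** The Data Analysis section of the Protocol article gives the comparative model in one sentence: "Linear regression models will be used to compare treatment and control outcomes while controlling for demographic variables such as age and gender". The Results section repeats the method without any covariates: "Linear regression (for continuous outcomes) will be conducted with interpretive qualitative methods".

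The baseline scores will be available. Outcome Evaluation states: "Assessments will be completed upon study entry and after weeks 4 and 8 of the program". Data Analysis mentions baseline data once, next to demographic data and for another purpose: "Baseline and demographic data from individuals who drop out will be compared to those who finish".

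The response variable is left open. Outcome Evaluation says: "The primary outcome measure will be the progression or regression of our participants’ mental health symptoms". This can be read as a follow-up score or as a change from study entry.

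On allocation, the Participants section says: "Participant allocation will be equally stratified (e-CBT, n=30; TAU, n=30". The wording describes equal arm sizes and names no stratification factor. Entry requires "a diagnosis of depression or anxiety secondary to a general medical condition", and no minimum questionnaire score is listed.

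**The concern.** In a randomised trial with a questionnaire score as outcome, the baseline value of the same score usually explains more of the follow-up variation than age or gender does. The article names the class of covariates to be used, and that class leaves the baseline score out.

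Baseline spread may be considerable here, because patients can qualify through depression or through anxiety; someone who enters with anxiety alone may start with a low depression score. This is inferred from the eligibility wording, as the article gives no score distribution.

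Two things are at stake in a trial of 60. The standard error of the treatment effect is larger than it needs to be. And if the arms differ by chance at entry, neither the allocation as described nor the model as stated deals with the difference properly.

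**Working it through.** **Inputs from the Protocol article.** 30 patients per arm (Participants); dropout of up to 30%, no imputation, and 20 per arm at a 5% level with power 0.95 (Data Analysis).

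**Assumptions, because the article gives no figure.** Correlation r between baseline and follow-up score of 0.4 to 0.6 (wider range 0.3 to 0.7); PHQ-9 standard deviation (SD) of 5 points (range 4 to 6), equal at both times, so that the slope of follow-up on baseline equals r.

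**1. The plan's own figures.** 20/(1 − 0.30) = 28.6, so 29 per arm, which agrees with the 30 planned. 30 × 0.70 = 21 evaluable per arm. The figure of 20 cannot be reproduced, since no SD or baseline mean is given. It implies a standardised difference of (1.960 + 1.645) × √(2/20) = 1.14 (two-sided, normal approximation), or 1.17 with the t distribution.

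**2. Variance of the treatment contrast**, in units of 2·SD²/n:
- week-8 score, unadjusted: 1
- change from baseline, unadjusted: 2(1 − r)
- follow-up score adjusted for baseline: 1 − r²

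The adjusted variance is smaller than the first by r², and smaller than the second by 2(1 − r) − (1 − r²) = (1 − r)². Both are positive for any r between 0 and 1.

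| r | Week-8 score | Change | Adjusted | Cut vs week-8 | Equivalent patients | Cut vs change | Equivalent patients |
|---|---|---|---|---|---|---|---|
| 0.4 | 1 | 1.20 | 0.84 | 16% | 1/0.84 = 1.19 | 30% | 1.20/0.84 = 1.43 |
| 0.5 | 1 | 1.00 | 0.75 | 25% | 1/0.75 = 1.33 | 25% | 1.00/0.75 = 1.33 |
| 0.6 | 1 | 0.80 | 0.64 | 36% | 1/0.64 = 1.56 | 20% | 0.80/0.64 = 1.25 |

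Over r = 0.3 to 0.7, the cut is 9 to 49% against the week-8 score and 35 to 15% against change.

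**3. Power, for illustration.** 21 per arm, two-sided 5%, noncentral t, true difference 0.8 SD, one degree of freedom charged for the baseline covariate, age and gender left out. Week-8 score: 0.716. Change: 0.637, 0.716, 0.807 at r = 0.4, 0.5, 0.6. Adjusted: 0.788, 0.831, 0.885.

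**4. Chance imbalance.** The standard error of the baseline difference is √(2/21) = 0.31 SD, which at SD 5 is 1.54 points. The probability of a difference above 0.5 SD in either direction is about 0.11 at 21 per arm.

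A baseline difference D shifts the unadjusted week-8 contrast by r·D and the change contrast by (r − 1)·D. With D = 1.54 and slope 0.5:
- week-8 score: 0.5 × 1.54 = +0.77 points
- change: (0.5 − 1) × 1.54 = −0.77 points

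At slope 0.5, an SD of 4 to 6 gives shifts of 0.62 to 0.93 points in size. With the baseline score in the model, this shift is removed.

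**The case against.** **The response is undefined.** A reader might infer that the model compares raw week-8 scores and that the gain is simply 19 to 56% more patients. The article does not support that. Its outcome wording and its 30% criterion for the PHQ-9 lean, if anything, towards change, and a change score already uses the baseline. This objection stands against any single figure: for change, the gain falls as r rises and the imbalance shift has the opposite sign. It does not remove the point, because adjustment is more precise than either response.

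**The article is condensed.** Its covariate list is open, and an unseen analysis plan may add the baseline score. But the list is open only within demographic variables, and the same section treats baseline and demographic data as separate things. The model as stated can therefore be improved; it is more than a detail left out. It would still be too strong to infer that the sponsor has decided against baseline adjustment, since nothing in the article excludes it.

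**Validity is not affected.** A reader might infer bias or an inflated false-positive rate. Neither follows: the unadjusted contrast is unbiased over randomisation. A shift of 0.77 points is half the standard error of the unadjusted week-8 contrast (1.54 points at SD 5), and its confidence interval already allows for such variation on average. What remains is lost precision, and a misleading estimate in those trials where the arms happen to differ at entry.

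**The gain is slightly overstated.** The factor 1 − r² compares with a model without covariates, whereas age and gender are already in. Any part of the baseline score that they explain does not count twice. Residual degrees of freedom would fall from 42 − 4 = 38 to 37. Both corrections are small.

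The week-4 assessment might suggest a repeated-measures analysis, but the article states only linear regression, so there is no such model to amend.

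**Conclusion.** The point holds as a free improvement to a stated model. It does not identify an error that invalidates the analysis. The direction of the gain does not depend on which response was meant, as long as the correlation lies between 0 and 1 and the SDs at the two times are similar.

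The size of the gain does depend on the response and on assumed values, so the figures for the two responses must be kept apart: 16 to 36% less variance against a raw week-8 score and 30 to 20% less against change, for r from 0.4 to 0.6. The imbalance figure of about 0.8 points further assumes SD 5 and slope 0.5. None of these values is in the article. The plan has limited room to give precision away, because its claimed power at 20 per arm already needs a standardised difference of about 1.14 to 1.17.

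**What to change.** Replace the model sentence in Data Analysis with: *Each follow-up score is analysed by linear regression with arm, the baseline value of the same score, age and gender as covariates.* State that the response is the score itself and not percentage change, which also settles the open question about the response.

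Qualifying diagnosis (depression, anxiety or both) could be added, since the Participants section has it confirmed before randomisation. This is optional: no gain has been computed for it, and each extra term uses degrees of freedom.

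The cost is one sentence and one degree of freedom per model, with no new data. The change should be made before outcome data are analysed.

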## Results

This study received funding in August 2020 and ethics approval from the Queen’s University Health Sciences and Affiliated Teaching Hospitals Research Ethics Board (file# 6031471) in February 2021. Participant recruitment has been conducted through social media advertisements, physical advertisements, and physician referrals. To date, 11 participants (e-CBT, n=5; TAU, n=4; dropout, n=2) have been recruited. Data collection is expected to conclude by December 2021, and data analysis is expected to be completed by January 2022. Linear regression (for continuous outcomes) will be conducted with interpretive qualitative methods. All protocols and results have been, and will be, reported using the GUIDED and TIDieR Report Checklists and Guidelines (Multimedia Appendices 1 and 2).

## Discussion

Previous studies have reported the efficacy of e-CBT in managing mood and anxiety disorder in the general population [13-15]. Based on these previous and promising results, showing efficacies comparable to face-to-face psychotherapy, web-based delivery of psychotherapy to patients receiving oncologic and palliative care who have comorbid anxiety or depression could be an effective treatment option. Using the predesigned therapy modules, an experienced care provider can deliver asynchronous care to 3-4 patients simultaneously for 1 synchronous session. This effectively implies that more service could be provided at a lower cost, effectively increasing the capacity and performance of the health care system by 4 folds. This would result in drastic shortening of wait times and increased coverage, leading to significant financial and societal cost savings. Our findings have the potential to be encoded into clinical policy and could potentially be used by family medicine clinics, specialists, and insurance companies as a new resource. To our knowledge, there have been no similar studies in this field. If successful, this innovation has the potential to propagate significant positive change.

## Appendix

Multimedia Appendix 1 GUIDED Report Checklist and Guidelines.

Multimedia Appendix 2 TIDieR Report Checklist and Guidelines.

Multimedia Appendix 3 Peer-review report by Queen's University Department of Psychiatry Internal Grant Competition 2020.

